#### Study design using PDI/RDS

As noted above, RDS begins with direct recruitment of a small number of initial seeds who start recruitment chains by recruiting their peers into the research [36, 38]. In the present study, initial seeds are randomized to an intervention or control arm at a 1:1 ratio. Further, eligible and consenting peers who are subsequently recruited into the study are assigned to the same arm as their recruiter. Thus each initial seed and the peers subsequently enrolled in his/her recruitment chain are considered a cluster. This cluster randomized controlled trial design is necessary because intervention activities begin at the time of recruitment, when recruiters educate peer recruits on core messages. Because the statistical power of a clustered trial increases with the number of clusters, we plan to recruit more seeds than is typical in RDS (namely 40 seeds per arm), with a target sample size of 3000 individuals. The PDI/RDS study component also includes those with previously diagnosed infection (called “known positives”), and will describe HIV health indicators and engagement in HIV care among this subgroup. Study activities are approved by the Institutional Review Board at the NYU School of Medicine, and the protocol is registered with clinicaltrials.gov (NCT01607541).

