##### Intervention session #2

Participants return for a second one-on-one intervention session two weeks after their initial session. During this session, CDC required pre-test counseling is provided to assess readiness and desire for testing. If participants decide to test, standard consent is obtained, followed by the OraQuick Advance Rapid HIV-1/2 Antibody Test with oral mucosal fluid. While the test is processing, subjects complete a computerized HIV prevention and risk-reduction program, called CARE for Prevention [56]. If the rapid HIV test is non-reactive, participants are counseled and provided referrals, and their involvement in the study is complete.

For reactive tests, a second OraQuick Advance Rapid HIV test is administered, similar to local health department protocols, to minimize false positive results on site [57]. An OraSure Western Blot confirmatory test is also conducted, with results available in 1-2 weeks. Participants are then asked to provide blood specimens for HIV viral load and CD4 testing. Because some newly diagnosed participants decline to provide blood at diagnosis, they may do so at a future contact if they so choose. Navigation (described below) may begin at this point for intervention arm participants who have serious barriers to engaging in future study activities, including meeting to receive confirmatory results, or the session may end after the blood specimen is provided and navigation may begin at Session 3.

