#### Data analysis

The hypothesis for the main Treat and Retain aim is that compared with participants in the control arm, PDI arm participants will be more likely to 1) attend an HIV clinic appointment sooner; 2) initiate ART earlier; 3) achieve viral load suppression; and 4) be retained in HIV care during the 12-month follow-up period. Logistic regression will be used to compare groups on viral load suppression. Since HIV viral load assay results range from <50 to >100,000 copies/ml, other generalized linear models will examine intervention impact on median viral load, log transformed viral load, and on viral load dichotomized at 1,000 or 10,000 copies/ml, which have been associated with greater HIV transmission risk [68–71]. Cox proportional hazards regression will compare groups on time to first HIV clinic appointment and initiation of ART if indicated. Frailty models [72, 73] will examine intervention effects on first HIV clinic appointment and initiation of ART with participants clustered by recruitment chain. Covariates for these analyses will include prior HIV testing and initial viral load.

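### CD4 comes from the same specimen as initial viral load but is not a named covariate; prespecifying it could add power, mainly for time to ART

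*Protocol article*

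**What the plan says.** The Data analysis section of Part 1 sets the models. For suppression: "Logistic regression will be used to compare groups on viral load suppression". For the time-to-event outcomes: "Cox proportional hazards regression will compare groups on time to first HIV clinic appointment and initiation of ART if indicated". Frailty models by recruitment chain are added. The section then names two covariates: "Covariates for these analyses will include prior HIV testing and initial viral load".

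The section on intervention session #2 describes the blood draw after a reactive test: "Participants are then asked to provide blood specimens for HIV viral load and CD4 testing". Two further statements there bear on timing. Some people give no blood at that point: "Because some newly diagnosed participants decline to provide blood at diagnosis, they may do so at a future contact if they so choose". In one arm, the next component may already have started: "Navigation (described below) may begin at this point for intervention arm participants who have serious barriers to engaging in future study activities".

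The Part 1 power analysis is based on suppression. It gives N = 254 with a detectable OR of 2.07, and an effective n of 176 (ICC .20, 80 seeds) with a detectable OR of 2.39.

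**The concern.** CD4 is the other laboratory measure of disease state requested at diagnosis. The trial pays for it and accepts its companion value as a covariate, yet names it in no Treat and Retain model. In Cox and logistic models, leaving out a prognostic variable moves the arm coefficient toward zero even when the arms are balanced on it. With an effective sample of about 176 on the plan's own figure, there is little power to spare. If CD4 matters for starting ART or for reaching suppression, the plan forgoes power that it could have with no new data.

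**Working it through.** **Step 1: the plan's own figures.** Inputs are from the Study design and Power analysis sections.
- N = 3000 × 0.10 × 0.85 = 255 (stated 254).
- Mean chain size = 254 / 80 = 3.175. Design effect = 1 + (3.175 − 1) × 0.20 = 1.435. Effective n = 254 / 1.435 = 177 (stated 176).
- Detectable OR at 80% power, two-sided 0.05, 1:1, control rate 30%: 2.07 with 127 per arm and 2.39 with 88 per arm. Both match.

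These are unadjusted two-proportion figures, so the choice of covariates does not affect them.

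**Step 2: simulation at N = 254.** Individuals are independent and viral load is always in the model. Assumed, because the documents give none of it: CD4–viral load correlation −0.4, CD4 effect per SD from 1.0 (none) to 2.0, and, for Cox, an arm HR of 1.5, a baseline hazard of 0.08 per month and follow-up cut at 12 months (67 to 69% with an event). The logistic model uses a control rate of about 30% and a conditional OR of 2.07. There were 2,000 Cox and 3,000 logistic runs per row. Entries are mean arm coefficient (SE), then power.

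| Model | CD4 effect per SD | Without CD4 | With CD4 | Power without → with |
|---|---|---|---|---|
| Cox | 1.0 | 0.416 (0.153) | 0.418 (0.154) | 77.3 → 77.2% |
| Cox | 1.25 | 0.394 (0.153) | 0.404 (0.154) | 73.0 → 75.0% |
| Cox | 1.5 | 0.380 (0.154) | 0.405 (0.155) | 71.1 → 76.5% |
| Cox | 2.0 | 0.344 (0.155) | 0.407 (0.156) | 60.8 → 74.5% |
| Logistic | 1.0 | 0.734 (0.269) | 0.738 (0.270) | 78.2 → 78.3% |
| Logistic | 1.25 | 0.727 (0.270) | 0.739 (0.273) | 77.1 → 78.1% |
| Logistic | 1.5 | 0.718 (0.272) | 0.744 (0.277) | 75.1 → 76.7% |
| Logistic | 2.0 | 0.676 (0.273) | 0.737 (0.287) | 69.4 → 73.1% |

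The true coefficients are ln 1.5 = 0.405 and ln 2.07 = 0.728. The SE does not fall in any row. The gain comes from the coefficient: in the last Cox row the ratio to its SE goes from 0.344 / 0.155 = 2.22 to 0.407 / 0.156 = 2.61. In the rows with no CD4 effect, power changes by 0.1 point, well inside simulation error (√(0.77 × 0.23 / 2000) ≈ 0.9 points for a single power estimate).

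**Step 3: simulation at n = 176.** Same correlation, 1,200 to 1,500 runs per cell, baseline hazard 0.09 per month.
- Time to ART, assumed arm HR 1.65, HR per SD of CD4 of 0.74, 0.61 and 0.50: power 77 → 78%, 70 → 78% and 65 → 81%, gains of 1, 8 and 16 points.
- Suppression, conditional OR 2.39, three rising CD4 strengths: 78 → 79%, 76 → 77% and 73 → 77%, gains of 1, 1 and 4 points.

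Taken together, the gain is about 0 to 4 points for suppression and about 0 to 16 for time to ART. Time to first appointment was not simulated.

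**The case against.** The strongest reply is that nothing here is an error. The covariate sentence is open-ended: it says what the models will include and does not exclude CD4, and an article commonly leaves the full list to the SAP. That stands. CD4 is not named, but a reader may not infer that it has been ruled out.

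Second, the size is assumed. The documents give no prognostic strength for CD4 beyond viral load, and no hazard ratio or hazard for time to ART. The effective n of 176 was derived for suppression and is borrowed for time to ART. The large gains appear only where a strong CD4 effect is assumed. ART initiation is also analysed only where indicated; indication is not defined, and if it depends on disease stage, part of CD4's value is already used up. All of this stands, and it is why only a range is given.

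Third, the logistic simulations hold 2.07 and 2.39 fixed as conditional odds ratios, whereas the plan's figures are unadjusted. The falling power in the column without CD4 therefore says nothing against the power statement. The comparison within a row uses the same simulated data and remains fair.

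Fourth, this CD4 is not strictly a baseline value. The draw follows the first session (and, for recruited intervention-arm peers, peer education), and it may come later, after navigation has begun in one arm. That stands too, but initial viral load has the same problem and is already accepted. It calls for one timing rule for both values; it is no reason to pass over CD4.

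**Conclusion.** The point holds as an optional efficiency improvement. CD4 is requested in the same specimen as an accepted covariate and is not named in the models. Not adjusting for it forgoes about 0 to 4 points of power for suppression and about 0 to 16 for time to ART, depending on an assumed CD4 effect and an assumed correlation of −0.4 with viral load. If CD4 adds nothing beyond viral load, including it costs next to nothing.

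Three stronger readings are tempting, and the documents do not support them:
- That the comparisons lose precision. The SE is flat or slightly higher with CD4 in the model.
- That the arm comparison is biased by chance imbalance in disease stage. Chance imbalance under randomisation is already allowed for in the test's error rate, and no imbalance in CD4 is documented.
- That the power statement is wrong because CD4 is missing from it. That statement uses no covariates and reproduces at a 30% control rate.

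**What to change.** In the Data analysis section, or in the SAP before outcome data are seen:
- Prespecify CD4 from the diagnosis specimen, as a continuous term, alongside initial viral load, at least in the time-to-ART and suppression models.
- Count either value as initial only if the specimen was drawn before navigation or ART began.
- Handle missing CD4 by the same rule as missing initial viral load.

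No new data are needed. The cost is one more model term and some late-drawn specimens treated as missing; the documents do not say how many. Because only the intervention arm receives navigation, the cut-off may remove more values there, so the shared missing-data rule should keep those participants in the analysis. While viral load is already a covariate, adding CD4 from the same specimen should lose few or no further participants.

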#### Power analysis

We estimate 10 % of all participants will be newly diagnosed with HIV infection and assume an attrition rate of 15 % at the last follow-up among those with newly diagnosed HIV infection (*N* = 254). We estimate the smallest detectable difference in proportion between PDI and control arms given a desired power of 80 % and α = .05. Assuming 15-45% of control participants achieve HIV viral load suppression within 12 months, odds ratio of 2.07 are detectable. With an ICC as high as .20 due to clustering by 80 seeds, the effective sample size is *n* = 176 and odds ratios of 2.39 are detectable.

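### The detectable odds ratios of 2.07 and 2.39 hold for control suppression of about 30% to 45%, but not for the lower half of the stated 15-45% range

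*Protocol article*

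**What the plan says.** The Protocol article, Part 1 (Treat and retain phase), Power analysis, sets out the smallest detectable effect "given a desired power of 80 % and α = .05". The analysed number is built from "with a target sample size of 3000 individuals" (section Study design using PDI/RDS), then "We estimate 10 % of all participants will be newly diagnosed with HIV infection", and it goes on to "assume an attrition rate of 15 % at the last follow-up". This leads to the stated 254 newly diagnosed participants.

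The claim at issue is "Assuming 15-45% of control participants achieve HIV viral load suppression within 12 months, odds ratio of 2.07 are detectable". The next sentence repeats it for the clustered case: "With an ICC as high as .20 due to clustering by 80 seeds", the effective sample size is put at 176 and the detectable odds ratio at 2.39. The section names no single control rate and does not say whether the test is one- or two-sided.

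**The concern.** A range of control rates is paired with a single odds ratio. On a plain reading, an odds ratio of 2.07 (or 2.39 with clustering) can be detected with 80% power wherever the control rate falls between 15% and 45%. That cannot be so. With the odds ratio fixed, a lower control rate means fewer events, a less precise log odds ratio and less power.

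The Aims section makes the Treat and Retain comparison the main aim, and viral load suppression is the outcome for which Part 1 gives a power calculation. If few controls reached suppression, a null result would be read as coming from a comparison with 80% power when the real figure for the stated odds ratio was lower.

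**Working it through.** **Inputs from the Protocol article.** Target 3000; 10% newly diagnosed; 15% attrition; 80 seeds; ICC 0.20; α = .05; power 80%; control suppression 15-45%. Under Study design using PDI/RDS, "initial seeds are randomized to an intervention or control arm at a 1:1 ratio".

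**Assumptions.** Two-sided test; equal arms among the newly diagnosed (127 per arm for 254, 88 per arm for 176).

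**Step 1: the sample sizes.**
- 3000 × 0.10 × 0.85 = 255 (stated 254).
- Mean cluster size 254/80 = 3.175. Design effect 1 + (3.175 − 1) × 0.20 = 1.435. Effective n = 254/1.435 = 177.0 (stated 176).

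Both reproduce within rounding. The problem is not in the sample sizes.

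**Step 2: the formula.** For control rate p0 and odds ratio OR:
- p1 = OR·p0 / (1 − p0 + OR·p0), and p̄ = (p0 + p1)/2
- Power = Φ{ [ (p1 − p0) − 1.96·√(2p̄(1 − p̄)/m) ] / √([p0(1 − p0) + p1(1 − p1)]/m) }, with m per arm.

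**Step 3: reproduce the stated figure at 30%, OR 2.07, m = 127.**
- p1 = 0.621/1.321 = 0.4701; difference 0.1701; p̄ = 0.3851.
- Pooled SE = √(0.4736/127) = 0.0611; unpooled SE = √(0.4591/127) = 0.0601.
- Power = Φ[(0.1701 − 1.96 × 0.0611)/0.0601] = Φ(0.84) = 79.9%.

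Solving for 80% power at 30% gives 2.072 with N = 254 and 2.388 with n = 176. Both published values match at the midpoint of the stated range.

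**Step 4: the same odds ratio at 15%.**
- p1 = 0.3105/1.1605 = 0.2676; difference 0.1176; p̄ = 0.2088.
- Pooled SE = √(0.3304/127) = 0.0510; unpooled SE = √(0.3235/127) = 0.0505.
- Power = Φ[(0.1176 − 1.96 × 0.0510)/0.0505] = Φ(0.35) = 63.6%.

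**Step 5: the whole range.**

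| Control rate | Power for OR 2.07, N = 254 | OR needed for 80% | Power for OR 2.39, n = 176 | OR needed for 80% |
|---|---|---|---|---|
| 15% | 63.6% | 2.38 | 64.9% | 2.78 |
| 20% | 71.8% | 2.22 | 72.7% | 2.57 |
| 25% | 76.9% | 2.13 | 77.4% | 2.46 |
| 30% | 79.9% | 2.07 | 80.1% | 2.39 |
| 35% | 81.6% | 2.04 | 81.4% | 2.35 |
| 40% | 82.2% | 2.03 | 81.7% | 2.34 |
| 45% | 81.9% | 2.03 | 81.2% | 2.36 |

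Reaching 80% power at 15% would take about 374 analysed participants for OR 2.07 (against 254), or an effective 252 for OR 2.39 (against 176).

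**Step 6: does another method rescue the range?** No.
- Exact chi-square power at 15% is 63.8% and 65.8%.
- Unpooled, arcsine, Wald log-odds and continuity-corrected versions need odds ratios of 2.36 to 2.48 at 15% with N = 254, and 2.74 to 2.94 with n = 176.
- A one-sided test at 15% gives 74.8% and 75.9%.

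**The case against.** Several things can be said for the protocol.

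- **Half the range is sound.** A reader might infer that the two odds ratios are right only at 30% and wrong elsewhere. That goes too far. The claim is that these odds ratios are detectable, and from 30% to 45% they are, with a small margin in the upper part. At 25% the shortfall is only about 3 points. The material gap is at roughly 15-20%.
- **Low control rates are not shown to be the likely ones.** A reader might also infer that newly diagnosed people will fall in the lower half, so that the trial is underpowered in practice. The documents do not support this. The section Testing, linkage, and retention for HHR gives 30% with undetectable viral load among all Americans living with HIV, which is the rate at which both figures reproduce. The Background puts 18% of infected persons as unaware of their status. If, as an assumption, none of them is suppressed, the rate among the diagnosed is 30/82 = 37%, where power is about 82%. Controls are also referred to care with phone reminders (Intervention session #3) and have 12 months to reach suppression. Against that, the same section on testing and linkage says that African Americans/Blacks and Latinos do worse on every indicator, but it gives no figure. The question stays open.
- **Condensed wording.** The authors may have calculated at the midpoint and printed the plausible range beside it. The numbers fit that explanation exactly. Even so, the printed sentence attaches the odds ratio to the whole range.
- **Scale.** The section first speaks of a detectable difference in proportions. On that scale the detectable difference with N = 254 is smaller at 15% (14.6 points) than at 30% (17.0 points). The fault is specific to quoting a constant odds ratio.
- **Sidedness is not stated.** With a one-sided test, power at 20% would be 81.5% and 82.2%, which narrows the gap. At 15% it would still fall short.

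These points limit the reach of the finding. None of them makes the statement true at the 15% that the protocol itself names.

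**Conclusion.** The statement is wrong as written for control rates below about 30% and right from about 30% to 45%. At the lower bound the type II error for the stated odds ratios is about 35-36% instead of 20%.

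This rests on a two-sided 5% test and equal numbers of newly diagnosed participants per arm. Randomization is by seed, so equal arms are not guaranteed, and an unequal split would generally lower power further.

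No sample size or decision rule depends on the sentence. The analysed number follows from the enrolment target, the diagnosis rate and attrition. This is a correction to a stated operating characteristic, and the documents give no basis for saying that the trial will in fact have low power.

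**What to change.** Replace the single values with ranges, for example: *for control suppression of 15-45%, the detectable odds ratio is at most 2.38 (2.03 to 2.38) with N = 254, and at most 2.78 (2.34 to 2.78) with an effective n of 176.* Alternatively, keep 2.07 and 2.39 and tie them explicitly to a control rate of 30% or, within the stated range, higher. Either version should state whether the test is two-sided.

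The cost is one sentence. Design, sample size and analysis do not change. The stated detectable effect becomes less favourable at the low end of the range.

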## Part 2: Seek and test phase

### Introduction

#### Study aims

The aim of the Seek and Test Phase is to compare the relative yield and efficiency of RDS, described above, and venue-based sampling (VBS) to seek out and identify previously undiagnosed HIV infection among HHR, and to project the clinical impact, costs, and cost-effectiveness of these two strategies (as shown on Fig. 4). Although the NHBS uses both VBS and RDS methods, they have not yet been directly compared in terms of their efficacy and cost-effectiveness to identify undiagnosed HIV among HHR in the U. S. The present study addresses this gap in the literature by conducting VBS and RDS in the same geographical location, namely, the core HRA, and targeting the same underlying population of HHR.

**Fig. 4 Fig4:**
[figure not shown]
Seek and Test Phase

#### Venue-based sampling (VBS)

VBS is a method to systematically recruit individuals in a target population who may be hard-to-reach, but who may be located and engaged in identifiable venues such as parks and hair salons. VBS has proven successful in identifying populations at high risk of HIV infection, mainly MSM [74–76], but also heterosexuals in the U.S. and globally [77, 78]. VBS starts by identifying days and times at which the target population gathers at specific venues, constructing a sampling frame of venue-day-time units (VDTs), randomly selecting and visiting VDTs (the primary sampling units), and systematically intercepting and collecting information from consenting members of the target population [74].

#### Hypotheses and endpoints

We hypothesize a higher proportion of newly diagnosed participants will be recruited by RDS than VBS, after controlling for socio-demographic differences between the samples. This is because RDS is designed to reach deep into hidden or wary populations, engaging the more isolated or vulnerable network members who may not be present in social venues [61]. Indeed, peers have credibility that can foster engagement with research studies more effectively than direct recruitment by research staff, even for those with multiple barriers to HIV testing [62].

## Methods

### Defining and identifying specific venues within the HRA

Once the core HRA had been defined, as we described above, we identified venues within it to establish the locations and times for sampling. A venue is defined as a public space where a threshold number of the target population may congregate or pass through [76]. Typically VBS studies target discrete venues such as churches, hair salons and barbershops, recreational centers, bars, city parks, parks or street corners outside public housing facilities, and grocery stores [76]. While members of the target population naturally congregate in these locations, these types of venues may require the permission of a manager or other gatekeeper before recruitment. Indeed, parks and public housing are regulated by the local authorities, and private venues can close during the study period. Thus targeting these types of venues is labor-intensive.

However, the population density, built environment, and population transportation dynamics of central Brooklyn suggested an alternate means of defining a venue, namely, as city blocks where the target population congregates or passes through. But since central Brooklyn is geographically large (70.82 sq. miles) and densely populated (2.6 million) [79], we needed to narrow the scope of potential venues to reduce redundancy and increase study efficiency.

To select specific venues for sampling during the study’s planning phase, we drew on Department of Urban Planning geographic data showing the location, land use (residential vs. commercial), and other attributes of every building in Brooklyn [80]. With this, we defined a “venue” as any city block within the core HRA with >70 % commercial land use. Study staff then reviewed a random sample from this sampling frame to qualitatively assess whether this approach would yield sufficient foot traffic for study recruitment. To supplement this block approach, we also included public parks and public housing projects as discrete venues for sampling.

Venue-day-time periods (VDTs) were chosen for each venue. VDTs were defined as four-hour blocks where a sufficient number of the target population passes through the venue. For each venue defined above, we included a morning, afternoon, and evening VDT for potential recruitment. This ultimately yielded a sampling frame of 394 block venues and 75 park and housing project venues available for random selection during the study, each with 3 associated time periods.

